### **Inclusion Criteria**

Women aged 18 to 75 years; right-handed, literate, with a confirmed diagnosis of fibromyalgia (FM) according to the criteria of the American College of Rheumatology (2010-2016). These criteria required assessment using the widespread pain index (WPI) and the symptom severity score (SSS). Specifically, participants needed either a WPI score of at least seven, or a score between 4 and 6 accompanied by an SSS of 9 or higher or widespread pain in four out of five regions along with specific symptoms such as abdominal pain, depression, and headache within the last six months. In general, a combined WPI and SSS score of 13 or more was necessary as per the ACR-2016 standards. Moreover, participants were required to report a minimum score of 6 on the Numerical Pain Scale (NPS), which ranges from 0 to 10, for most days over the previous three months. They also had to agree not to change their doses of antidepressant and anticonvulsant medications during the study.

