### g. Randomization

Using the website [www.sealedenvelope.com](http://www.sealedenvelope.com), random numbers were employed to fairly distribute 112 patients into two groups: those who would receive anodal transcranial direct current stimulation (a-tDCS) or sham transcranial direct current stimulation (s-tDCS) over the dorsolateral prefrontal cortex (DLPFC). The allocation ratio was based on susceptibility to the placebo response, determined by the reduction in the NPS (0-10) from pre- to after one session of s-tDCS. Participants were classified as responders if their NPS (0-10) decreased by 30% or more or non-responders if it was less than 30%. This fair process resulted in a 1:1:1:1 allocation ratio, with 56 patients receiving a-tDCS (28 responders and 28 non-responders) and 56 patients receiving s-tDCS (28 responders and 28 non-responders). To prevent predicting the next patient's allocation, randomization was performed in 10 blocks of twelve. Prior to the recruitment phase, two investigators who were not involved in the patients' assessments performed the randomization. The randomized numbers were placed in sealed, brown envelopes with the patient's entry sequence number written outside. The engineer responsible for programming the intervention device opened the envelope only after the patient had provided informed consent.

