## Statistical Analysis

Continuous and categorical variables were compared using Fisher's exact test, the chi-square test, and the t-test for independent samples. The Shapiro-Wilk normality test was applied to determine the normal distribution of continuous variables. A Linear Mixed-Effects Regression Models for Repeated Measure (LMM) assessed primary outcomes (pain severity and disability) with treatment, placebo response (responder vs. non-responder), time, and the treatment-by-time interaction as fixed effects, and included a random intercept for patients to account for time differences. If appropriate, we then performed the Bonferroni's Test adjustment for post hoc multiple comparisons to identify differences between the groups at each time point and used a paired t test to assess the effects on each experimental group. The Generalized Linear Model (GLM) was used to examine the treatment effect on the secondary outcomes including quality of life, HPT, PGI-I and the descending pain inhibitory system (DPIS). The treatment effect on primary and secondary outcomes was adjusted for analgesic use and placebo susceptibility. Analgesic use was included in the model to control a potential confounder affecting pain outcomes. This ensures that the observed effects of a-tDCS and s-tDCS are attributable to the interventions rather than variations in analgesic use, thereby enhancing the validity of the results. All analyses were adjusted for multiple comparisons using Bonferroni's Test. The modified ITT (m-ITT) analysis included those completing  $\geq 50\%$  of sessions, with missing data imputed using regression model coefficients. In the m-ITT, with an adjusted protocol, encompassing all patients who completed at least ten sessions. The choice of ten sessions for ITT was guided by most of the literature supporting clinical symptom improvement in chronic pain. This method is not as strict as classical ITT, but it suggests that A-tDCS could be useful in clinical settings with at least a minimum number of sessions. Specifically, we replaced missing values with imputed data derived from a regression model using observed data. The treatment group served as the predictor, and the outcome variable with missing values was imputed based on regression coefficients, indicating the relationship between the treatment group and the outcome. This imputation method was applied, for example, to ten patients who withdrew after ten tDCS sessions. Sensitivity analyses confirmed consistent LMM results with or without imputation ([see per-protocol analysis in results - Supplement II](#)).

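### Within-arm paired t tests are said to assess effects in each group, but change from baseline in one arm is not a treatment effect in this design

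*Protocol*

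**What the plan says.** The Statistical Analysis section of the protocol analyses the primary outcome with a linear mixed model. Its terms are treatment, placebo response, "time, and the treatment-by-time interaction as fixed effects, and included a random intercept for patients". If appropriate, Bonferroni-adjusted comparisons follow: "post hoc multiple comparisons to identify differences between the groups at each time point". The same sentence then adds that the team "used a paired t test to assess the effects on each experimental group". The section does not say which two visits are paired, that these tests are descriptive only, or that their p-values must not be compared between arms.

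Three other places bear on what such a test would pick up:

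- Section g (Randomization) sorts patients by their response to one sham session: "Participants were classified as responders if their NPS (0-10) decreased by 30% or more".
- Under Inclusion Criteria, entry depends on high pain on most days of the preceding three months: "participants were required to report a minimum score of 6 on the Numerical Pain Scale (NPS".
- Sections f.4 and j describe exercise and pain education given with both active and sham stimulation. The item on analgesic use allows extra medication as needed.

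The Statistical Analysis section also states that treatment effects are adjusted for analgesic use and placebo susceptibility, and that "All analyses were adjusted for multiple comparisons using Bonferroni's Test".

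**The concern.** A paired t test within one arm asks whether the mean has moved since baseline. The protocol names several causes of movement other than active stimulation: sham response, the shared exercise and education, and changes in analgesic intake. Regression to the mean after entry on high pain may add to these. None of them is removed by looking at one arm alone. Randomisation against sham removes those that act equally in both arms, and only a between-arm contrast uses it.

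Two misreadings become easy. One is that active stimulation worked because its arm changed significantly. The other is that active differs from sham because only one arm reached p < 0.05. Neither is evidence of a difference between arms. The paired test also leaves out the analgesic adjustment that the same section presents as protecting the validity of the results.

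**Working it through.** **The plan's own figure.** The sample size in section f.4 is for a between-arm difference of 0.6 points at moment 5, with 80% power and a two-sided 5% level. The repeated-measures formula behind the protocol's R code is n per arm = (φa·SDa² + φb·SDb²)(z₀.₉₇₅ + z₀.₈₀)²/δ². The AR(1) matrices and retention rates give φa = 1.0597 and φb = 1.0629.

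- n = (1.0597 + 1.0629) × (1.960 + 0.842)²/0.36 = 46.3, so 47 per arm and 94 in all, as stated.
- For 15% dropout, 47/0.85 = 55.3, so 56 per arm and 112 in all, as stated.

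The trial is therefore sized on a between-arm contrast. Within-arm change plays no part in it.

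**Inputs for the within-arm test.**

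- n = 56 per arm (section g) and SD = 1 in each arm (section f.4).
- Baseline-to-moment-5 correlation, from the corner of each R matrix: 0.0256 active, 0.0016 sham. The values 0.4 and 0.2 in the text are the adjacent-visit parameters of the two arms.
- Two-sided 5% level, not yet Bonferroni-adjusted.
- My assumptions: baseline is paired with moment 5, and the true mean change d is the same in both arms, so there is no treatment effect. The documents give no expected change, so d is varied.

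**Formulas.**

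- SD of change = √(2(1 − ρ)): active √(2 × 0.9744) = 1.396; sham √(2 × 0.9984) = 1.413.
- Standard error = SD/√56: active 0.187; sham 0.189.
- The chance of a significant result comes from the noncentral t with 55 degrees of freedom, noncentrality d/SE and critical value 2.004.
- P(exactly one arm) = pA(1 − pS) + pS(1 − pA).

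Example, d = 0.4: noncentrality is 2.14 (active) and 2.12 (sham), so pA = 0.558 and pS = 0.548. Then P(exactly one) = 0.558 × 0.452 + 0.548 × 0.442 = 0.494.

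| Common change d | Sham significant | Exactly one arm significant |
|---|---|---|
| 0 | 5% | 9.5% |
| 0.2 | 18% | 30% |
| 0.3 | 35% | 45% |
| 0.4 | 55% | 49% |
| 0.5 | 74% | 38% |
| 0.6 | 88% | 21% |
| 1.0 | >99% | 0.1% |

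In 20,000 simulated trials per setting, a direct between-arm test of change was significant in 4.8% to 5.2% at d = 0, 0.3, 0.4 and 0.5, as it should be.

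**Sensitivity, d = 0.2 to 0.6.**

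- With 47 per arm, sham is significant in 16% to 81% and exactly one arm in 27% to 50%.
- With a correlation of 0.5 in both arms and 56 per arm, the ranges are 31% to 99% and 1% to 48%.

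**Effect of Bonferroni.** The protocol does not state the number of tests in the family. At an illustrative level of 0.01, exactly one arm is significant in 12%, 42% and 42% of trials at d = 0.2, 0.4 and 0.6. A stricter level moves the peak to larger changes and does not remove it.

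**The case against.** The best defence is that no efficacy conclusion is planned from these tests. The mixed model with its treatment-by-time term is the primary analysis, and the paired tests sit in a conditional post hoc sentence after the between-group comparisons. The sample size and the standardised effect size are both between-arm. In a translated document, effects on each group may simply mean change within each group. All of this stands, and it limits the weight of the point. A reader might infer that the trial's main conclusion rests on within-arm p-values; the documents do not say so.

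Four other strong readings are tempting and also fail:

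- **A known amount of regression to the mean.** Entry is on the NPS, over most days of three months. The primary outcome is BPI interference, the mean of seven items. The documents give no correlation between the two, so the amount cannot be fixed and could be small. The argument does not need it, because sham response and the shared co-interventions are enough.
- **A correlation of 0.2 to 0.4 between baseline and follow-up.** The R matrices give far lower values at moment 5, and these are the ones used above.
- **Loss of incomplete cases.** The plan imputes missing values by regression, so the paired test need not drop patients. Whether that imputation is sound is a separate matter.
- **A causal claim about each arm.** The protocol says of the analgesic adjustment: "This ensures that the observed effects of a-tDCS and s-tDCS are attributable to the interventions rather than variations in analgesic use". This concerns confounding by analgesics. It is not a statement that within-arm change measures the effect of stimulation.

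It can also be said that Bonferroni covers all analyses. It does change the rates, and the unadjusted figures do not describe the plan exactly. It controls how often a change is declared, not what the change means.

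**Conclusion.** The point holds as a fault in a secondary clause. The paired t test does not measure what the protocol says it measures. With no difference between arms and an assumed common change of 0.2 to 0.6 points, the sham test is significant in about 18% to 88% of trials and exactly one arm in about 21% to 49%, against about 5% for a direct between-arm test. These figures rest on 56 per arm, SD 1, the protocol's matrices, unadjusted 5% tests and an assumed size of change. The one-arm-only risk peaks near 0.4 points. With a common change near 1 point both arms are almost always significant, and the risk is then that a significant change under sham, or under active, is read as an effect of stimulation. The between-arm mixed model, the sample size and the primary inference are not affected. The clause should be changed, but it does not undermine the trial's main analysis.

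**What to change.** Delete the paired t tests from the Statistical Analysis section. Report the change in each arm from the mixed model with its confidence interval, labelled as description and without a p-value. State that every claim of a treatment effect rests on the mixed model's between-arm contrast at the stated time point, with its confidence interval, and that significance in one arm will not be compared with significance in the other. The cost is the loss of the within-arm p-values. Sample size and data collection do not change.

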### f.4. Sample size estimation

The primary outcome of this study, pain-related function, is measured using the 7-item Brief Pain Inventory (BPI) interference scale. This scale serves as a Multidimensional Pain Interference Index (MPII), providing a comprehensive view of how pain affects various dimensions of an individual's life, including emotional well-being, social interactions, and daily activities. Focusing solely on pain severity may fail to reflect the full impact of pain on a person's overall quality of life. The secondary outcome, pain intensity, is evaluated using the 2-item BPI severity scale. Both BPI scales range from 0 to 10, with higher scores representing worse function or intensity. Understanding the Minimal Clinically Important Differences (MCID) changes in pain interference scores is vital for clinicians to determine whether changes are significant enough to indicate meaningful improvements or declines in quality of life, rather than just being statistically significant. According to previous studies in chronic pain populations, an MCID of approximately 0.7 points for both the BPI interference and severity scales has been identified. However, consensus guidelines have established a 1-point difference as the MCID for both scales, while a 30% reduction from baseline is also recognized as a significant indicator of moderate improvement. In examining the effects of E-PNE with a-tDCS and s-tDCS groups at the final time point (moment 5), which occurs three months post-treatment, a more conservative MCID of 0.6 points was used for estimating the sample size. This cautious approach aims to ensure a thorough evaluation of the study's power to assess the treatment effects. The sample size estimation was performed using the PSS *Health tool* 32. [https://hcupa-unidade-bioestatistica.shinyapps.io/PSS\\_Health/](https://hcupa-unidade-bioestatistica.shinyapps.io/PSS_Health/). To detect a minimum difference of 0.6 points between the means of the Multidimensional Pain Interference Index (MPII) for the a-tDCS group and the s-tDCS group at the final time point (moment 5) in a repeated measures analysis, a sample size of 94 participants (47 per group) was calculated. To account for a potential dropout rate of 15%, the sample size was increased to 112 participants. This calculation was based on an

assumed 80% power, a 5% significance level, and relevant parameters for the treatment group.

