Standard deviation of 1 unit

- Retention rates of 99%, 98%, 96%, and 94% at moments 2, 3, 4, and 5, respectively
- Autoregressive correlation matrix for MPII by BPI of 0.4 for the **a-tDCS** group

For the **s-tDCS** :

- Standard deviation of 1 unit
- Retention rates of 99%, 98%, 96%, and 94% at moments 2, 3, 4, and 5
- Autoregressive correlation parameter of 0.2.

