## j. Methods

The study protocol is outlined in the figure of timeline the study (**figure 2**), showing the assessments conducted at each stage.

The tDCS device used in the study was developed in collaboration with the Biomedical Engineering department of the Hospital de Clínicas de Porto Alegre (HCPA), Brazil. It is registered on the Brazilian National Health Surveillance Agency (ANVISA) under registration number N°80079190028. This device, designed for home use, has demonstrated its effectiveness in several trials .

Key features of the device include the ability to monitor contact impedance and automatically stop the session if impedance exceeds 1 mA for more than 5 seconds or if there is an electric current fluctuation greater than 10%. The device also logs the time and duration of each session, ensuring patient adherence. Since July 2020, it has been commercially available through Quark Medical (Brazil).

[figure not shown]

**Figure 2.** Timeline the study.

**Protocol Components:** The stimulation sites for the study include anodal tDCS with the anode placed over the left dorsolateral prefrontal cortex (DLPFC) (F3) and the cathode over the right DLPFC (F4). Additional components of the protocol involve pain education and physical exercise. The device features a high resistance and alarm system to adjust the cap and add saline, as well as monitoring curves of current intensity versus impedance for both active (a-tDCS) and sham (s-tDCS) stimulation.

**Assessments:** Participants completed a baseline questionnaire covering clinical and socio-demographic characteristics, analgesic use, heat pain threshold (HPT), and pain pressure threshold (PPT) assessed via quantitative sensory testing (QST).

**Instruments:** The study utilized several validated instruments, including the Fibromyalgia Impact Questionnaire (FIQ), Central Sensitization Inventory (CSI-BP), Beck Depression Inventory (BDI-II), Brazilian Pain Catastrophizing Scale (BP-PCS), Pittsburgh Sleep Quality Index (PSQI), and the Brazilian Portuguese version of the Profile of Chronic Pain: Screen (B-PCP).

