### **Clinical Measurements: Included assessments of depressive symptoms, central sensitization, sleep quality, analgesic use**

- x. Demographic Data and Medical Comorbidities: Collected via a standardized questionnaire.
- xi. Psychological Assessments: Included the Pittsburgh Sleep Quality Index (PSQI)  and the Central Sensitization Inventory for the Brazilian Population (CSI-BP)  with scores indicating symptom severity. Depressive symptoms were assessed using the Beck Depression Inventory II, and the Pain Catastrophizing Scale (PCS) evaluated catastrophic thinking about pain .

- xii. Analgesic Use: Patients were allowed to take additional medications as needed and were instructed to record their intake in diaries. The total dose taken each week during the treatment period and three-month follow-up were used for analysis.

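### The treatment effect is adjusted for analgesic use as a confounder, but the variable described is most likely as-needed dose taken after randomisation, and adjusting for that can bias the total effect

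*Protocol*

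**What the plan says.** Three statements in the protocol bear on this.

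- **The adjustment.** Statistical Analysis says: "The treatment effect on primary and secondary outcomes was adjusted for analgesic use and placebo susceptibility". The reason given is: "Analgesic use was included in the model to control a potential confounder affecting pain outcomes". The claimed benefit is: "This ensures that the observed effects of a-tDCS and s-tDCS are attributable to the interventions rather than variations in analgesic use".
- **The variable.** Item xii (Analgesic Use) under Clinical Measurements says: "Patients were allowed to take additional medications as needed and were instructed to record their intake in diaries". It continues: "The total dose taken each week during the treatment period and three-month follow-up were used for analysis".
- **A baseline item.** Section j (Methods, Assessments) lists analgesic use among the topics of the baseline questionnaire. Nothing links that item to a model.

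The sentence in Statistical Analysis that sets out the mixed model lists four fixed effects: treatment, placebo response, time and treatment by time. Analgesic use is not among them. It enters only through the later adjustment sentence, which names both primary and secondary outcomes. The one sensitivity analysis mentioned concerns imputation. No analysis without the analgesic term is described.

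**The concern.** A confounder of a treatment comparison is a common cause of treatment assignment and outcome. Randomisation removes such causes in expectation, so analgesic use cannot confound the comparison of arms. As-needed dose recorded after randomisation lies downstream of it. A patient in less pain will tend to take less, and a treatment that works can therefore lower intake.

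Conditioning on a consequence of treatment or of pain does two things. It takes out whatever part of the effect is expressed through intake. It also opens a path through unmeasured causes of both pain and medicine-taking, such as coping style or prescriber habits, which randomisation does not balance within levels of dose. The coefficient then estimates neither the total effect nor, without a further assumption of no unmeasured common causes, a direct effect. The protocol states neither a direct-effect target nor that assumption.

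At stake are the primary estimate and every secondary estimate that carries the same term.

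**Working it through.** **1. Inputs from the protocol.** Section f.4 plans for a 0.6-point difference in BPI interference at moment 5, SD 1 in each arm, autoregressive correlation 0.4 (active) and 0.2 (sham), retention falling to 94%, 80% power and 5% significance. Statistical Analysis specifies two-tailed tests. The protocol gives no correlation between analgesic dose and pain, and no expected effect of treatment on dose. Those two quantities are assumed below and varied.

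**2. The protocol's own figure.** With the repeated-measures formula behind its R call, the variance factors at moment 5 are 1.0597 (active) and 1.0629 (sham).

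n per arm = (1.0597 + 1.0629) × (1.960 + 0.842)² / 0.6² = 2.1226 × 7.849 / 0.36 = 46.28, so 47 per arm and 94 in total. For dropout, 47 / 0.85 = 55.3, so 56 per arm and 112 in total. Both figures reproduce. The R call contains no covariate, so the planned 0.6 points is a total effect. The sample size itself is not affected by this point.

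**3. What the adjustment does.** Write a for the reduction in dose caused by treatment (in SD of dose) and b for the within-arm slope of pain on dose (points per SD). Then

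adjusted effect = total effect − a × b.

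With outcome SD 1, b is also the within-arm correlation, so the residual SD is √(1 − b²): 0.98, 0.92 and 0.80 for b = 0.2, 0.4 and 0.6. Correlation between arm and dose inflates the variance by 1 + a²/4: 1.00, 1.01 and 1.0625 for a = 0, 0.2 and 0.5. Power comes from a two-sided t test with 47 per arm and standard error √(1 − b²) × √[(2/47)(1 + a²/4)]. Unadjusted, 0.6 / √(2/47) = 2.91, which gives about 82%.

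| Assumed dose reduction a | Slope b | Adjusted effect 0.6 − ab | Power |
|---|---|---|---|
| 0 | 0.2 / 0.4 / 0.6 | 0.60 / 0.60 / 0.60 | 84% / 88% / 95% |
| 0.2 SD | 0.2 / 0.4 / 0.6 | 0.56 / 0.52 / 0.48 | 78% / 77% / 82% |
| 0.5 SD | 0.2 / 0.4 / 0.6 | 0.50 / 0.40 / 0.30 | 66% / 53% / 42% |

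At a = 0 there is no bias and some gain in precision. At 0.2 SD the power barely changes, yet the estimate shrinks by 7 to 20% (0.04/0.6 to 0.12/0.6). At 0.5 SD it shrinks by 17 to 50% (0.10/0.6 to 0.30/0.6).

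**4. A second mechanism: dose simply follows pain.** If within-arm correlation is ρ and treatment affects dose only through pain, the adjusted effect is 0.6 × (1 − ρ²): 0.58, 0.50 and 0.38 for ρ = 0.2, 0.4 and 0.6. A simulation of 2,000,000 records gave 0.576, 0.504 and 0.385. With 94% of 47 per arm retained, power is 79%, 73% and 62%, against 80.5% unadjusted.

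**5. The other direction.** If the within-arm slope is −0.3, a reduction of 0.2 or 0.5 SD gives 0.6 + 0.06 = 0.66 or 0.6 + 0.15 = 0.75, away from zero.

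**The case against.** The best defence is that the covariate may be baseline use. The adjustment sentence gives no time point, item xii says the weekly doses were analysed but not that they were the model covariate, and baseline analgesic use was collected. Baseline use would be a legitimate covariate. This stands as a caution: the on-treatment reading joins two sections. It is still the likelier reading, because the weekly on-study dose is the only analgesic quantity said to be analysed, and the stated aim of excluding variations in analgesic use fits doses that move during the trial. A SAP, which was not available, might settle the time point. The confounder rationale would remain wrong for an on-study dose.

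The mixed-model term list also omits analgesic use, so one could argue that the primary model does not contain it. The later sentence names primary outcomes explicitly, so the text is inconsistent rather than clear.

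A reader might infer more: that the primary estimate is certainly biased, that the bias is towards no effect, or that the randomised comparison is lost. The protocol does not support this. There is no bias if treatment leaves dose unchanged, and a negative slope pushes the estimate away from zero. A reader might also compute power of 65%, 47% and 29% for the 0.5 SD case by keeping the residual SD at 1. That overstates the loss, because a slope large enough to cause the bias also explains outcome variance.

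Finally, the section is in the past tense and reports completed sensitivity analyses, so a change means re-analysis and not only new wording. That is fair.

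**Conclusion.** The point holds in conditional form. It is firm that the protocol adjusts the primary and secondary treatment effects for analgesic use, calls it a confounder, and claims that this secures attribution to the intervention. It is probable, not certain, that the covariate is as-needed dose taken after randomisation. On that reading the rationale is wrong, and the adjusted coefficient can be biased for the total effect.

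Size and direction cannot be fixed from the protocol. Under the assumed positive slopes, a true 0.6-point effect is estimated anywhere from 0.60 (no change in dose) to 0.30 (0.5 SD reduction, slope 0.6). These figures are illustrations that rest on assumed dose shifts and slopes and on the planning SD of 1.

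The point does not extend to placebo susceptibility. It is classified from one sham session and used in the allocation, and it is a proper covariate.

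**What to change.** - Remove on-treatment and follow-up analgesic dose from the primary mixed model and from the secondary generalised linear models.
- If an analgesic covariate is wanted, use baseline use and say so explicitly. Check first in what form it was recorded, since section j does not say it was a dose.
- Analyse weekly analgesic dose by arm as an outcome in its own right. This answers directly whether the arms differed in intake.
- Keep any model adjusted for on-study dose only as a labelled exploratory analysis, and drop the claim that it secures attribution to the intervention.
- Make the list of mixed-model terms agree with the adjustment sentence. Keep placebo susceptibility.

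No new data are needed. The cost is a small re-run of the primary and secondary analyses and the loss of whatever precision the covariate gave. If results are already known, report the change openly and show the estimates with and without the term.

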#### **R code:**

```
Ra <- matrix(data = c(1, 0.4, 0.16, 0.064, 0.0256, 0.4, 1, 0.4, 0.16, 0.064, 0.16, 0.4, 1, 0.4, 0.16, 0.064, 0.16, 0.4, 1, 0.4, 0.0256, 0.064, 0.16, 0.4, 1), nrow = 5, byrow = TRUE)
Rb <- matrix(data = c(1, 0.2, 0.04, 0.008, 0.0016, 0.2, 1, 0.2, 0.04, 0.008, 0.04, 0.2, 1, 0.2, 0.04, 0.008, 0.04, 0.2, 1, 0.2, 0.0016, 0.008, 0.04, 0.2, 1), nrow = 5, byrow = TRUE)
longpower::power.mmm(Ra = Ra, ra = c(100, 99, 98, 96, 94)/100, sigmaa = 1, Rb = Rb, rb = c(100, 99, 98, 96, 94)/100, sigmab = 1, delta = 0.6, lambda = 1, sig.level = 5/100, power = 80/100)
```

| Minimum detectable difference | Standard deviation Treatment | Standard deviation Control | Significance level (%) | Power (%) | Ratio of sample size | Sample size Treatment | Sample size Control | Sample size |
|-------------------------------|------------------------------|----------------------------|------------------------|-----------|----------------------|-----------------------|---------------------|-------------|
| 0.6                           | 1                            | 1                          | 5                      | 80        | 1                    | 47                    | 47                  | 94          |
| 1                             | 1                            | 1                          | 5                      | 80        | 1                    | 17                    | 17                  | 34          |
| 1.4                           | 1                            | 1                          | 5                      | 80        | 1                    | 9                     | 9                   | 18          |
| 1.8                           | 1                            | 1                          | 5                      | 80        | 1                    | 6                     | 6                   | 12          |
| 2.2                           | 1                            | 1                          | 5                      | 80        | 1                    | 4                     | 4                   | 8           |
| 2.6                           | 1                            | 1                          | 5                      | 80        | 1                    | 3                     | 3                   | 6           |

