
The standardized difference means (SDM) was used to compute the effect size (ES) by dividing the mean difference between a-tDCS and s-tDCS by the pooled baseline standard deviation (SD). The ES was interpreted as small if lower than 0.20 to 0.49, moderate if between 0.50 and 0.79, and large if larger than 0.80^54. All statistical analyses were performed using two-tailed tests at the 5% significance level with SPSS, version 22.0 (SPSS, Chicago, IL).

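### The sample size assumes an undivided 5% level for the moment-5 contrast, while the analysis section applies Bonferroni to all analyses over an unstated family, so the stated 80% power may not hold

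*Protocol*

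**What the plan says.** **Sizing (Protocol, f.4. Sample size estimation).** The target is a 0.6-point difference between arms on the seven-item BPI interference score, "at the final time point (moment 5) in a repeated measures analysis, a sample size of 94 participants (47 per group) was calculated". The text gives an "assumed 80% power, a 5% significance level, and relevant parameters for the treatment group". The R call confirms the undivided level: "delta = 0.6, lambda = 1, sig.level = 5/100, power = 80/100". The total is raised from 94 to 112 for 15% dropout, and section g. Randomization allocates 56 per arm.

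**Analysis (Protocol, Statistical Analysis).** A linear mixed model with treatment, placebo response, time and treatment-by-time terms is fitted. A conditional next step is a Bonferroni "adjustment for post hoc multiple comparisons to identify differences between the groups at each time point". Later in the same section comes the unconditional sentence "All analyses were adjusted for multiple comparisons using Bonferroni's Test". The section closes with a general level: "All statistical analyses were performed using two-tailed tests at the 5% significance level with SPSS, version 22.0".

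The protocol does not give the number of comparisons in the Bonferroni family. It does not say that the moment-5 contrast is tested outside that family, and the sample size makes no allowance for the adjustment.

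**The concern.** The contrast that was powered is also one of the per-time-point group comparisons that the analysis section says are Bonferroni-adjusted. If the adjustment runs across visits, that contrast is tested at 0.05/k, whereas its power was computed at 0.05. A true 0.6-point effect would then be missed more often than the 20% implied, and a null result could be read as coming from an adequately powered trial when it did not.

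The error runs in one direction. Bonferroni costs power and does not raise the false-positive rate.

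**Working it through.** **Inputs, all from f.4. Sample size estimation and its R code, except the allocation.** Difference 0.6; SD 1 in each arm; retention 100, 99, 98, 96 and 94% at moments 1 to 5; autoregressive correlation 0.4 (a-tDCS) and 0.2 (s-tDCS); two-sided 5%; 80% power; 56 per arm randomised (g. Randomization). The number of comparisons, k, is not in the protocol and is an assumption.

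**Step 1: reproduce the protocol's figure.** For a repeated-measures comparison at the last moment with attrition:

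n per arm = (φa + φb) × (z(1−α/2) + z(power))² × SD² / δ²

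Here φ is the last diagonal element of the inverse information matrix. That matrix sums, over dropout patterns, the share of patients in the pattern times the inverse of the correlation matrix of the moments they complete. The inputs give φa = 1.0597 and φb = 1.0629, a sum of 2.1226.

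n = 2.1226 × (1.960 + 0.842)² / 0.36 = 46.28, so 47 per arm and 94 in total, as stated. Power at 47 per arm is 80.6%. For dropout, 47/0.85 = 55.3, so 56 per arm and 112 in total, also as stated. The arithmetic of the sizing is correct at α = 0.05.

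**Step 2: choose plausible values of k.** The schedule of assessment has BPI at baseline, weeks 1 to 4 and three months, which is five post-baseline visits. The sizing uses five moments, the first with 100% retention, which leaves four after baseline. Four and five are therefore the natural across-visit families. Two, three and six are shown for range. k = 1 corresponds to a correction within each visit, because two arms give one pair.

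**Step 3: power at 56 randomised per arm.** Power = Φ(0.6/SE − z(1 − 0.05/(2k))).

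- Modelled 94% retention: SE = √(2.1226/56) = 0.1947, so 0.6/SE = 3.082.
- 15% dropout, completers only: 56 × 0.85 = 47.6 per arm, SE = √(2/47.6) = 0.2050, so 0.6/SE = 2.927.

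| k | Level 0.05/k | z | Power, 94% retention | Power, 15% dropout |
|---|---|---|---|---|
| 1 | 0.0500 | 1.960 | 86.9% | 83.3% |
| 2 | 0.0250 | 2.241 | 80.0% | 75.4% |
| 3 | 0.0167 | 2.394 | 75.4% | 70.3% |
| 4 | 0.0125 | 2.498 | 72.0% | 66.6% |
| 5 | 0.0100 | 2.576 | 69.4% | 63.7% |
| 6 | 0.0083 | 2.638 | 67.1% | 61.4% |

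For k = 5 with 94% retention, for example: 3.082 − 2.576 = 0.506, and Φ(0.506) = 69.4%.

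**Step 4: scale.** The Step 1 formula at α = 0.01 gives n = 68.86, so 69 per arm before dropout inflation, against 47 in the protocol. The inflation to 56 does not close that gap.

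**The case against.** **The family is not stated.** A correction for group differences at each time point can mean a correction over pairs of arms within a visit. With two arms that is one comparison, and the stated power holds. This reading is open on the text and stands as a limit on the conclusion. Its weakness is that the stated adjustment would then do nothing to the between-group comparison.

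**The per-visit comparisons are post hoc and conditional.** They follow the mixed model and are made only where appropriate. That is true of the first Bonferroni statement, but the later blanket sentence carries no such condition. No other test of the moment-5 contrast is described. If the overall treatment-by-time interaction were the confirmatory test, the sizing would not match that either.

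**Multiplicity families belong in the SAP.** Often so. Here, however, the protocol itself fixes both a blanket rule and a sample size, and the two are not aligned.

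**The practical loss is small for larger effects.** The sizing section calls 0.6 conservative, below the 0.7 and 1 point it cites as important differences. At k = 5, power for 0.7 is Φ(0.7/0.2050 − 2.576) = about 80% with 15% dropout and Φ(0.7/0.1947 − 2.576) = about 85% with modelled retention. For 1 point it is about 98% even at 47 per arm (SE = √(2.1226/47) = 0.2125). This stands and limits the consequence, but the protocol's power claim is for 0.6.

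**Stronger readings that the document does not support.** A reader might divide by ten or twelve, pooling visits with the two outcomes that the analysis section calls primary and perhaps counting baseline. Nothing in the protocol pools outcomes into one family or tests baseline within it. A reader might also quote 60% power, which is the k = 5 result at 47 per arm with 94% retention. Since 56 per arm are randomised, 47 already reflects 15% dropout, and applying the retention rates again counts attrition twice.

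**Conclusion.** The point holds as a mismatch between sizing and analysis, not as a miscalculation: 94 and 112 are both reproduced. The 80% power for 0.6 points is secured only at an undivided two-sided 5%, and the blanket Bonferroni sentence does not leave the powered contrast at that level.

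The size of the loss depends on an assumed k. Under the across-visit reading, power with 56 per arm is about 67–72% for four visits and 64–69% for five, so a true 0.6-point effect would be missed about 31–36% of the time with five. With two comparisons it is 75–80%, and with a within-visit correction there is no loss. These figures rest on the protocol's SD of 1, its correlations, and attrition between the modelled 6% and the 15% allowed for.

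**What to change.** State the Bonferroni family: which time points and outcomes share the correction, and whether the moment-5 BPI interference contrast is in it. Then restate the power for 0.6 points at the resulting level, about 64–69% if the family is five visits. If the correction was meant only within each visit, say so; the stated power then stands. This costs a sentence or two and needs no patients or data.

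The alternative is to name the moment-5 BPI interference contrast as the single primary test at two-sided 5%, and to confine Bonferroni to the other time points and the secondary outcomes. That matches the sizing, but it is not free. The Statistical Analysis section already reports ten withdrawals after ten sessions and the outcome of sensitivity analyses, so lifting the correction now would relax the level on the primary contrast with data in hand. It is acceptable as a pre-specified rule only with documentation that it was fixed before unblinded data were seen. Otherwise it should be disclosed and labelled as post hoc.
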